## Abstract

**Background:**

Different methods are available for the treatment of venous ulcers. Most current approaches focus on a combination of topical and compressive therapy. Adjuvant low-level laser therapy may be helpful in lesions with a protracted healing course, but evidence for its use is still limited. This paper describes the protocol of a randomized controlled trial designed to compare the effect of adjuvant low-level laser therapy versus conventional venous ulcer tissue repair, evaluated by a nurse using clinical indicators from the Nursing Outcomes Classification (NOC).

**Methods/design:**

For this prospective randomized controlled trial, 40 adult patients of both sexes with active venous ulcers will be recruited. Subjects will be selected by the sealed-envelope method without any annotation or external identification that might refer to the type of study group. At the time of unblinding, a label with the description of the group to which the patient belongs (that is, control or intervention) will be found inside the envelope. Conventional treatment (topical medication and compressive therapy) will be offered to both groups. Additionally, the intervention group will receive adjuvant low-level laser therapy. All patients will be followed weekly until ulcer healing or for a maximum of 16 weeks. Evaluation of tissue repair will be based on 14 clinical indicators drawn from NOC for wound healing (secondary intention) and tissue integrity (skin and mucous membranes). The primary endpoint will be decreased wound size and scar formation. This laser therapy is expected to enhance the quality, speed, and effectiveness of the treatment of venous ulcers, a chronic condition. This should reduce associated costs to the health service and allow patients to resume their daily activities sooner.

**Discussion:**

This randomized clinical trial will use a validated method to investigate the effect of a novel intervention for the treatment of venous ulcers.

**Trial registration:**

ClinicalTrials.gov, NCT03229330. Registered on July 2017.

**Electronic supplementary material:**

The online version of this article (10.1186/s13063-018-2729-x) contains supplementary material, which is available to authorized users.

## Background

Chronic venous insufficiency can be defined as the set of clinical manifestations caused by reflux and/or obstruction of the peripheral venous system (superficial, deep, or both), usually affecting the lower limbs [1]. Clinical examination and a taking thorough history, which usually reveal clinical manifestations attributed to venous involvement (such as tingling, pain, burning, muscle cramps, edema, pruritus, restless legs, and fatigue), are the first steps in diagnosis. Diagnostic accuracy can be enhanced with Doppler ultrasonography, a noninvasive imaging modality that evaluates the anatomy of the venous system and its physiology by a hemodynamic evaluation of blood flow [2]. The consequences of chronic venous insufficiency include edema, hyperpigmentation of the skin, and, often, development of superficial, irregularly shaped venous ulcers.

Venous ulcers represent about 70–90% of all leg ulcers, with a lifetime prevalence of 0.1% to 2% in the world population. Incidence is higher in individuals over 65 years of age, and women are proportionally more affected, due to their higher survival rates compared to men [3, 4]. The natural history of a venous ulcer is a continuous cycle of healing and tissue derangement that can persist for a long time, with substantial morbidity and recurrence in approximately 70% of cases [3, 4]. The negative impact of venous ulcers on quality of life and the high costs associated with their treatment mean there is a pressing need for new therapeutic options. Conventional venous ulcer treatment is currently based on a combination of topical care (wound dressing) and compressive therapy, as well as educating patients on self-care, which includes wound dressing, hygiene, diet, and exercise [5, 6].

Low-level laser therapy (LLLT) has been used as an adjuvant to conventional therapy with promising results, especially in patients with acute and bloody ulcers [7–9].

### Low-level laser therapy

Proper wound care requires dressings that provide an ideal environment for the wound bed and the healing process, with properties such as hydration, thermal insulation, elimination of necrotic tissue, bacterial control, and adequate pH level [7–9]. Thus, the dressing and medication need to be appropriate to the type of tissue injured, so that they can have the intended healing effect. When using a conventional topical medication, numerous factors may interfere with its action on the treated tissue. In this context, conventional care can be augmented with new technologies in an attempt to minimize this interference and potentiate wound healing. LLLT is a promising adjuvant wound-care technology, which may produce additional beneficial effects in tissue regeneration.

LLLT is a form of phototherapy that employs electromagnetic radiation capable of generating enough energy to interact with living tissues. It produces photochemical and photophysical effects without generating heat, with the intention of reestablishing cell homeostasis. Essentially, light energy is delivered topically in a controlled, safe manner and it is absorbed by photo-absorbers (chromophores) that transform it into chemical energy [8]. Positive effects include acceleration of tissue repair, increased formation of granulation tissue, wound contraction, inflammation modulation, and pain reduction [7, 8]. The biochemical effects of LLLT are associated with the release of preformed substances (histamine, serotonin, and bradykinin), which stimulate the production of ATP and inhibit the production of prostaglandins. Moreover, the bioelectric effects of laser light improve the functioning of the sodium–potassium pump (Na^+^/K^+^-ATPase, which is responsible for maintenance of the cell membrane potential), again increasing the production of ATP. The resulting energy is used to normalize cellular and tissue functions according to normal tissue genetics and physiology, thus promoting more consistent tissue repair [7–10].

Although several studies have demonstrated positive outcomes with LLLT, little is known about its beneficial effects on the treatment of chronic wounds such as venous ulcers. A systematic review of four randomized clinical trials in which laser therapy was administered to patients with a diabetic foot ulcer over 2 to 16 weeks found favorable outcomes regarding ulcer size and time to healing [7]. Another randomized clinical study of 51 patients with leprosy wounds reported a clinical improvement with LLLT, although there was no statistically significant difference between the control group (CG) and intervention group (IG) [11].

These trials notwithstanding, evidence is still limited, with most coming from observational studies. The authors of these studies note that more robust research is still needed to enable standardization of parameters and expansion of LLLT to other clinical scenarios, such as venous ulcers. Additional randomized clinical trials are particularly necessary to bridge this knowledge gap [12–16].

### Evaluation of tissue regeneration

The monitoring of tissue regeneration is based on a nurse’s clinical judgment regarding the characteristics of the wound in relation to its bed, its edges, and the perilesional skin. This evaluation guides the choice of wound-care medication to be used, but is susceptible to evaluator error, because there are no standardized clinical indicators.

The evaluation of tissue regeneration can be enhanced using classification systems. Among such systems, the Nursing Outcomes Classification (NOC) is particularly interesting as it provides a list of clinical indicators for evaluating a patient’s condition and the clinical course. These indicators are scored on 5-point Likert scales (range 1 to 5), in which the lowest score represents the worst possible state and the highest score represents the most desirable state after implementation of interventions [9–17]. However, research into the clinical applicability of the NOC in wound evaluation is still incipient, which makes it impossible for nurses to know which clinical indicators to measure during the clinical follow-up of patients with venous ulcers. This randomized clinical trial should provide clinical evidence of the effect of LLLT as an adjuvant treatment for venous ulcers when compared to conventional topical treatment. Intervention effects and clinical evolution will be assessed through a reliable, validated method, namely, the clinical indicators of the NOC.

The aim of this article is to describe the protocol of a randomized controlled trial designed to compare the effect of conventional venous ulcer treatment with adjunctive LLLT versus conventional treatment alone. Throughout, patients will be evaluated with the clinical indicators described in the NOC.

## Methods/design

### Study design and centers

This randomized clinical trial will be conducted on a sample of participants recruited from the outpatient clinics of Hospital de Clínicas de Porto Alegre (HCPA), a tertiary-care center affiliated with the Federal University of Rio Grande do Sul, Brazil. At HCPA, patients with venous ulcers receive care from nurses, who perform nursing consultations with a focus on wound dressing and patient education. This study is conducted in accordance with the Standard Protocol Items: Recommendations for Interventional Trials (SPIRIT) Checklist (Additional file 1 and Fig. 1).

**Fig. 1 Fig1:**
[figure not shown]
Schedule of enrollment, interventions, and assessments of the low-level laser therapy intervention

### Inclusion and exclusion criteria

The study will include adult subjects (age ≥ 18 years) of both sexes with an established diagnosis of chronic venous insufficiency and an active venous ulcer. All must also be available to attend the outpatient clinic weekly.

Exclusion criteria include a body mass index consistent with grade 3 obesity, current treatment for cancer, erysipelas, cellulitis, lymphangitis, chronic lymphedema, immunosuppressant and/or corticosteroid therapy, a circular venous ulcer, and coagulation necrosis covering more than 25% of the wound bed.

The following exclusion criteria were adopted because the conditions increase the average time to chronic wound healing even further, and would, thus, require a longer follow-up period than specified for the study: circumferential ulcers, due to their large extent; lymphangitis, erysipelas, and cellulitis, because they prolong the inflammatory phase of the wound and, consequently, hinder the tissue repair process; morbid obesity, because it hinders cellular nutrition and can make it difficult for patients to complete the proposed exercises and change their own dressings; and finally, active treatment for cancer because it is an established contraindication to laser therapy.

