### Demographic and clinical variables

A structured questionnaire will be administered to all study participants to obtain sociodemographic and clinical information (age, sex, educational attainment, current medications, comorbidities, smoking, alcoholism, chronic venous insufficiency grade, ulcer duration, wound dressing regimen, nutrition, and exercise). Evaluation of the ulcer itself will be performed using the 14 NOC clinical indicators described above. Patients will be instructed to perform daily plantar flexion and extension and calf-strengthening exercises, resting in between, and taught how to dress their wounds as appropriate to their individual needs.

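### Ulcers of any age may enter and ulcer duration is recorded, but the stated primary comparison of the arms does not adjust for it

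*Protocol article*

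**What the plan says.** All places are in the protocol article.

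- **Inclusion and exclusion criteria.** Entry requires an "established diagnosis of chronic venous insufficiency and an active venous ulcer", adult age and availability for weekly visits. There is no minimum or maximum ulcer age and no requirement that earlier treatment has failed. Several conditions are excluded "because the conditions increase the average time to chronic wound healing even further, and would, thus, require a longer follow-up period than specified".
- **Demographic and clinical variables.** The baseline questionnaire includes "chronic venous insufficiency grade, ulcer duration, wound dressing regimen, nutrition, and exercise".
- **Independent/exposure and confounding variables.** The confounders to be controlled, by monitoring, are drug treatment and co-interventions given elsewhere. Ulcer duration is not among them.
- **Statistical analyses.** Weekly indicators are compared by generalized estimating equations (GEE). The mean scores for decreased wound size and scar formation are compared by Student's t-test. Ulcer characteristics are compared between the arms by a Mann-Whitney test. No covariate is named for any of these.
- **Randomization; Sample size.** Patients draw sealed envelopes, with a target of 20 per group. No stratification is described.

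**The concern.** How long an ulcer has been open at entry is a natural marker of how readily it will close. If so, it is prognostic for both primary indicators, wound size and scar formation. The entry criteria let this factor vary freely, the trial is small, and the allocation does nothing stated to balance it.

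If one arm happens to receive more long-standing ulcers, an unadjusted t-test carries that difference into the estimated laser effect. The reader would see the imbalance in the baseline table but would have no planned estimate that allows for it. An adjustment added after the imbalance is seen would be open to the charge of being chosen for its result.

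**Working it through.** **1. Role of ulcer duration at each step of the plan**

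| Step | Role of ulcer duration |
|---|---|
| Entry | None; any age qualifies |
| Allocation | No stratification stated |
| Baseline data | Recorded |
| Confounders to be controlled | Not listed |
| Primary between-arm test | Not in the t-test |
| Weekly GEE | No covariate named |
| Mann-Whitney on ulcer characteristics | May be included, as description only |

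The article gives no figure on this point to reproduce. It also does not give the mix of ulcer ages expected, so that mix must be assumed.

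**2. Chance of a sizeable imbalance**

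Inputs: 20 per arm (Sample size section); share p of long-standing ulcers (assumed); a gap of 20 percentage points, which is 0.20 × 20 = 4 patients.

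Let A and B be the numbers of long-standing ulcers in the two arms, each Bin(20, p). For p = 0.5, A + (20 − B) follows Bin(40, 0.5), and A − B ≥ 4 is the same event as A + (20 − B) ≥ 24. So

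P(|A − B| ≥ 4) = 2 × P(Bin(40, 0.5) ≥ 24) = 0.268, about 27%.

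For other shares, I summed the product of the two binomial probabilities over all pairs with |A − B| ≥ 4:

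| Assumed share p | P(gap ≥ 20 points) |
|---|---|
| 20% or 80% | 0.16 |
| 30% or 70% | 0.23 |
| 40% or 60% | 0.26 |
| 50% | 0.27 |

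The other way to count is to fix the 40 ulcers enrolled and split them 20:20 at random (hypergeometric). With exactly 20 of 40 long-standing, the chance is 0.34. With 12 or 28 of 40 it is 0.30, and with 8 or 32 of 40 it is 0.24. The 27% is therefore not the least favourable way to count.

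**3. The same check on a continuous scale**

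For a baseline variable in SD units, the standard error of the difference between arms is √(2/20) = 0.316. The chance of a difference above 0.3 SD is 2 × (1 − Φ(0.3/0.316)) = 0.34. Above 0.5 SD it is 2 × (1 − Φ(0.5/0.316)) = 0.11. Neither figure needs a cut-off for long-standing.

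**4. What such a gap would do to the estimate**

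If long-standing and recent ulcers differ by D points on an indicator under the same treatment, a gap of 0.20 between arms shifts the unadjusted difference by 0.20 × D. The article gives no D. For assumed values of 0.5, 1 and 1.5 points the shift is 0.1, 0.2 and 0.3 points, against the 1-point difference the trial is sized for.

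**5. How much a treatment-by-duration estimate could tell**

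Assume SD 1 (the article cites its SD without giving a number), 17 evaluable per arm and half of the ulcers long-standing, so 8.5 per cell. The standard error of the interaction is √(4/8.5) = 0.69 points. The power for a full 1-point interaction is about 30%. That is too little to decide anything.

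**The case against.** **Chance imbalance affects every prognostic factor in a 40-patient trial.** A valid unadjusted test already allows for it on average. This stands: the t-test is not biased over repeated randomisations, and its error rate is not in question. The case for adjustment is precision, and protection against the particular imbalance that occurs.

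**The article is condensed, and adjustment is commonly left to the full protocol or SAP.** This stands for what the article leaves open, and a fuller document may add the covariate. But the article does name the test for the primary indicators and does give a list of confounders, and ulcer duration appears in neither. Ulcer duration cannot be called unused, because the Mann-Whitney comparison may include it.

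**The 27% rests on an assumed share and measures how often a gap occurs, not how much harm it does.** This also stands, which is why the range and the 0.20 × D conversion are shown.

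**A stronger reading is tempting.** The abstract says "Adjuvant low-level laser therapy may be helpful in lesions with a protracted healing course, but evidence for its use is still limited", while entry is open to recent ulcers and some conditions are excluded because "the conditions increase the average time to chronic wound healing even further". A reader might infer that the trial shuts out slow healers and fails to study its target lesions. The documents do not support that:

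- The stated aim is to "compare the effect of conventional venous ulcer treatment with adjunctive LLLT versus conventional treatment alone", without restriction by ulcer age.
- The named gap is that "little is known about its beneficial effects on the treatment of chronic wounds such as venous ulcers", which refers to venous ulcers as a class.
- The Background also reports promise "especially in patients with acute and bloody ulcers", so the rationale is not confined to protracted healing.
- The exclusions are named conditions. An ulcer of many years without them stays eligible.
- The Discussion already gives the exclusion of more complex patients as a limitation.

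A reader might also infer that ulcers healing in both arms dilute the effect by a calculable amount. The article gives no share of such ulcers. With weekly follow-up they still inform on speed of healing, so no dilution figure can be supported.

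**Conclusion.** The point holds as an improvement to the analysis; it does not show an error or a contradiction in the design. Ulcer duration is free to vary at entry and is collected, yet it has no stated role in the treatment comparison beyond a possible baseline description.

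The probability of a gap of 20 percentage points or more in long-standing ulcers is about 27% if half are long-standing, and 16% to 27% for shares from 20% to 80%. The consequence for the estimate depends on how strongly duration predicts the scores, which the article does not say; a shift of 0.1 to 0.3 points would follow from the assumed values above. All of this rests on 20 per arm, unstratified allocation, and ulcer duration being prognostic.

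**What to change.** - **Primary comparison.** Replace the unadjusted t-test on decreased wound size and scar formation with a covariate-adjusted model. The GEE already planned for the weekly indicators would serve. Include ulcer duration at entry, on the log scale, as a prespecified covariate. The t-test can remain as a supportive, unadjusted result.
- **Confounding section.** Add ulcer duration to the listed variables, so that this section and the analysis section agree.
- **Conclusion.** Report the distribution of ulcer duration by arm, and state the conclusion for the ulcer ages actually enrolled.
- **Effect by duration.** A treatment-by-duration estimate with its confidence interval may be shown as exploratory. It should not decide the conclusion.

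Cost: one model degree of freedom and a change of wording. Eligibility, visits and data collection stay as they are. The Trial status section reports enrolment as ongoing, so at that stage the change could still be made and dated before the analysis.

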### Ethical considerations

Participants will be given information about the study and will read and sign an informed consent form before entering the study. Continuity of conventional treatment after completion of the study will be ensured for both groups. After 6 months, all patients will meet with the study team, who will evaluate tissue repair and their lifestyle, and they will receive specific care to prevent recurrent or new ulcers. The study protocol (15–0634) was approved by the institutional review boards of the hospital and the university. The study will be conducted in accordance with the principles of the Declaration of Helsinki and in accordance with Brazilian Ministry of Health guidelines and legislation for research on human subjects.

### Sample size

The WINPEPI program, version 11.43, was used to calculate the sample size. A sample of 34 subjects (*n* = 17 per group) would be able to detect a 1-point difference on a NOC indicator score between group means (laser intervention versus conventional control) as significant. The indicators are scored on 5-point Likert scales (range 1 to 5), in which the lowest score represents the worst possible state and the highest score represents the most desirable state after implementation of interventions. A change in one level, i.e., one point on the Likert scale, characterizes a positive effect of the intervention implemented throughout the treatment study, according to mixed linear models and generalized estimating equations. The standard deviation common to the groups [18], with a statistical power of 80% and significance level of 5% were defined for the study. To account for possible refusals and losses to follow-up, the sample was oversized by 20%. Thus, 40 subjects (*n* = 20 per group) will be recruited.

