### Outcomes

#### Primary outcome

The primary outcome is decreased wound size and scar formation based on NOC outcome wound healing (secondary intention; 1103).Wound area in cm^2^ (measured as the product of the longest dimension in the cephalocaudal direction by the widest dimension), evaluated by a Likert scale, with 1 being the worst possible score and 5 the best possible score. Each Likert scale score of the Decreased wound size indicator has an operational definition that corresponds to the size in cm^2^.Wound covered with epithelial tissue (new pink or bright tissue that develops from the wound edges or as islands on the surface of the wound), evaluated by a Likert scale, with 1 being the worst possible score and 5 the best possible score.

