### Statistical analyses

Continuous variables will be expressed as mean and standard deviation or median and interquartile range according to the data distribution. Categorical variables will be expressed as absolute and relative frequencies. Generalized estimating equations will be used for comparisons between the weekly indicators, and the least-significance-difference post-hoc test will be used to assess the difference between weeks.

For quantitative variables with a normal distribution, the difference between the two groups will be compared by Student’s *t*-test. This test will also be used to analyze the means of the NOC results in relation to the decreased wound size and scar formation outcomes. The Pearson correlation coefficient will be used to evaluate the linear association between NOC results and primary outcomes. A nonparametric Mann–Whitney test will be used for comparison between the two groups regarding the characterization of ulcers.

To assess the effect size of the intervention, relative risks with 95% confidence intervals will be calculated. A two-tailed *P* < 0.05 will be considered statistically significant. All analyses will be performed in PASW Statistics, Version 18.0.

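### The sample size and analysis sections name different methods for the laser effect on the primary indicators and none is designated as deciding, so the 5% level and 80% power are not tied to any one analysis

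*Protocol article*

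**What the plan says.** The article describes the assessment of the laser effect in three places.

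- **Primary outcome.** "The primary outcome is decreased wound size and scar formation": two indicators, each scored 1 to 5. They are among the 14 indicators used to evaluate healing, with weekly monitoring until the ulcer heals or for at most 16 weeks (Study protocol).
- **Sample size.** The 34 patients (17 per group) are said to be enough to "detect a 1-point difference on a NOC indicator score between group means", with 80% power at the 5% level. A one-level change counts as a positive effect "according to mixed linear models and generalized estimating equations". The common standard deviation is taken from a cited source and not printed.
- **Statistical analyses.** "Generalized estimating equations will be used for comparisons between the weekly indicators". Of Student's t-test the section says: "This test will also be used to analyze the means of the NOC results in relation to the decreased wound size and scar formation outcomes". Then: "To assess the effect size of the intervention, relative risks with 95% confidence intervals will be calculated". One two-tailed P < 0.05 threshold covers everything. Mixed models do not appear, the t-test has no stated week, and no method is called primary.

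**The concern.** The two sections give different lists of methods for the same effect: mixed models and GEE in one, t-test and GEE (plus relative risks) in the other. These methods need not estimate the same quantity. A t-test on means compares the arms at one time. A repeated-measures model can give an average over weeks, a difference in slope or a difference at a chosen week. A relative risk compares proportions with some event.

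Two things depend on which one decides. With no deciding test, a positive finding is open to the charge that it was chosen among several results. And 80% power is a property of one contrast. If the verdict comes from another, a negative result cannot be read against it.

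**Working it through.** **1. The methods side by side**

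| Method | Sample size section | Statistical analyses section |
|---|---|---|
| Mixed linear model | named | absent |
| GEE | named | named, weekly indicators |
| Student's t-test | not named | named, the two primary indicators |
| Relative risk | not named | named, event undefined |

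Only GEE is in both. Neither section ranks the methods.

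**2. The plan's own figure**

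Inputs from the sample size section: difference δ = 1, 17 per group, 80% power, 5%. The analysis section adds that tests are two-sided. The SD σ is not given, so it is assumed.

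- Normal approximation: n per group = 2(1.96 + 0.842)²σ²/δ² = 15.7σ². This gives 11 for σ = 0.8, 16 for σ = 1.0 and 23 for σ = 1.2. It gives exactly 17 for σ of about 1.01 to 1.04.
- Exact t: noncentrality = δ/(σ√(2/n)) = 1/√(2/17) = 2.92 on 32 degrees of freedom. Power is 80.7% at 17 per group and 86.9% at 20 per group (σ = 1.0).

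So the figure fits a plain two-mean comparison if σ is about 1.0. The text states no within-patient correlation or number of visits as inputs.

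**3. Power if a 16-week average decided instead**

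Assume per-visit SD 1.0, equal correlation ρ between weeks, complete data and 17 per group. The variance of a patient's mean is multiplied by (1 + 15ρ)/16. A gap growing linearly to one point at week 16 averages (1 + 2 + … + 16)/(16 × 16) = 8.5/16 = 0.531 points.

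| ρ | Variance factor | Constant 1-point gap | Linear build-up to 1 point |
|---|---|---|---|
| 0.3 | 0.344 | over 99% | 73% |
| 0.5 | 0.531 | 97% | 54% |
| 0.9 | 0.906 | 84% | 35% |

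The same 17 patients per group can be well above or well below 80%, depending on the contrast and the time course.

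**4. Type I error if more than one test could count**

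Simulation with no laser effect: one indicator treated as normal, 16 weekly scores, 17 or 20 per arm, complete data, 20,000 runs per setting. Correlation was either equal at 0.5 or first-order autoregressive at 0.8. All contrasts were tested with t-based methods, each holding about 5% alone.

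| Success if significant on | Type I error |
|---|---|
| Final-visit t-test only | about 5% |
| t-test or 16-week average | about 8–9% |
| t-test or slope | about 9–10% |
| Any of the three | about 12–13% |

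GEE with an uncorrected robust standard error gives about 15–16% for any of the three. Such a test alone already runs at 6.2–6.9% at this sample size, so part of that excess is small-sample bias, not choice among tests. The lower figures isolate the choice.

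**The case against.** The two sections can be read as largely agreeing. The trial is sized on a difference in group means, the t-test is expressly assigned to the two primary indicators, and GEE is in both places. The mixed-model phrase is attached to the meaning of a one-level change, not to the sample size formula or a decision rule. The analysis section describes GEE in terms of weeks, so the average and slope contrasts above are readings of the text, and the relative risk has no defined event. The article is also condensed, and an analysis plan not shown may name the primary test.

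Much of this stands, and it rules out two stronger conclusions that a reader might draw.

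- *That the 5% and 80% fail.* They would fail only under a rule that any significant test counts, or if the deciding contrast has other power. No passage states such a rule. With one t-test at one week on one indicator fixed in advance and an SD of about 1.0, both are met.
- *That 34 patients prove a single-visit t-test was intended.* With the SD unprinted, the number cannot identify the analysis. At ρ = 0.5, a 16-week average with per-visit SD 1/√0.531 = 1.37 gives the same power for a constant gap.

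The conflict itself remains. The sample size section uses mixed models and GEE to characterize the intervention effect, which supports a between-arm reading of GEE, and the analysis section omits the mixed model and adds the t-test. An analysis plan that kept to either section's list would still differ from the other. This is a disagreement between stated methods, not a detail left out.

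**Conclusion.** The point holds as an inconsistency that should be corrected. The two sections disagree on how the laser effect on the primary indicators is established, and the stated error rate and power are attached to no designated analysis.

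Its size is conditional. For a two-mean comparison with an assumed SD of 1.0, the power is as stated. For a 16-week average it could lie anywhere from 35% to over 99%. Type I error for one indicator stays at about 5% if one test is fixed and rises to about 8–13% if two or three may count. These figures rest on assumed correlations, an assumed time course and complete weekly data, although follow-up ends when an ulcer heals. They show what is at stake, not what the trial's error rate is.

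**What to change.** Make the sample size and statistical analyses sections name the same single primary analysis, contrast and time point.

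1. **One deciding contrast.** For example, a repeated-measures model on the weekly scores with arm, week and arm-by-week, with the between-arm difference at week 16 as the primary contrast. A single t-test at a named week would also remove the conflict.
2. **Patients healed before week 16.** State which score they carry at that week, since monitoring stops at healing.
3. **The two primary indicators.** State one rule: both must be significant, either with the 5% level divided between them, or one named as primary.
4. **Other methods.** Label the remaining tests and the relative risk (with its event defined) as supportive.
5. **Power.** Print the SD, tie the one-point difference and the 80% to the chosen contrast and indicator rule, and restate the power if it differs.

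The cost is a few sentences and no new data. Enrollment was ongoing when the article was written, so the change should be made before outcomes are compared by arm. The downside is that success can no longer be claimed from the other tests, and the stated power may change.
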